### Randomization and blinding

There are two possible moments of randomization: preoperative or intraoperative. If minimally invasive DPS is planned, patients will be randomized the day before admission to either ASI (intervention) or splenectomy (control). ASI will be performed at the end of procedure. If minimally invasive SPDP is the intended approach, splenectomy will only be performed if splenic preservation cannot be achieved due to technical or safety reasons during the procedure. In such a case, intraoperative randomization for ASI or splenectomy will be carried out on the spot, by a local researcher.

This will result in three groups:Minimally invasive DPS with ASI (intervention)Minimally invasive DPS without ASI (control)Minimally invasive SPDP (control)

An online computer variable block randomization module between ASI and DPS in a 1:1 ratio will be used. Patients will receive a subject inclusion number and subject randomization number.

The current study is an open-label trial due to a variety of reasons. First, surgeons cannot be blinded when the study intervention precludes a surgical procedure. Second, the splenic function is not believed to be associated with specific “advantages” in the general population in Western countries. Hence, the patient may not have expectations of a better postoperative recovery with a functional spleen. Third, antibody count is an objective measurement that cannot be influenced by physicians, surgeons or patient’s attitude. As the design of the study is open label, with only outcome assessors being blinded, unblinding will not occur.

### Surgical technique

All patients will be allocated to undergo a minimally invasive DP. In case of predetermined SPDP, preservation of the spleen will always be attempted. In case of minimally invasive DP with splenectomy and ASI, minimally invasive DP with splenectomy will be performed according to the surgeon’s preference. At the end of the procedure, after retrieval of the specimen, ASI will be performed. The specimen is placed on a sterile field and about a third of the spleen, including capsule, is taken from the spleen. This part is cut into smaller pieces with a minimum total weight of 30 g [30]. These smaller pieces are weighted using a scale within a sterile field. As soon as 30 g of splenic tissue is reached, the fragments are placed into a newly created pouch of the greater omentum. Hemolock clips are used to create the pouch as well as for closure of the pouch after the splenic tissue is placed into the pouch. No vascular reconstruction is required. Postoperative care is based on enhanced recovery principles. Patients who undergo DPS, independent of ASI, will receive the standard of care according to national post-splenectomy guidelines that include lifelong prophylactic antibiotics and yearly influenza immunization [7].

### Primary outcome

The primary outcome is the clearance of polysaccharide encapsulated bacteria measured by titres of *Salmonella typhi*-specific antibodies just prior to vaccination 6 months after surgery and 4 to 6 weeks thereafter.

One 6-mL serum tube will be used for sample collection immediately prior to vaccination with Typhim Vi™. Pre-vaccination-specific antibody levels will be determined. The vaccine (Typhim Vi™, Sanofi Pasteur MSD) will be given immediately after taking baseline blood. The procedure for the second measurement of *Salmonella typhi*-specific antibody response is identical to the first one. Pre- and post-immunization serum samples are separated by centrifugation and subsequently stored in aliquots at ≤  − 20 °C until analysis. All samples will be shipped to the University Hospital Southampton and simultaneous performance of specific antibody testing will be carried out in the University Hospital Southampton after the last patient completes the 7-month follow-up period.

*Salmonella typhi*-specific antibodies are measured using a commercially available ELISA kit (VaccZyme™ Anti-S. typhi Vi human IgG EIA from The Binding Site Group Ltd., Birmingham, UK). Samples are run in duplicate following manufacturer instructions. The results of specific antibody levels to Typhim Vi™ are expressed as U/mL (normal range, 7.4–600 U/mL). The value of the response is given as the ratio between pre- and post-immunization antibody levels. A threefold increase between titres pre- and post-vaccination will be used to define a normal antibody response according to prior literature [31, 32]. Participants are advised not to have any other vaccinations during the study period.

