## Background

The spleen initiates immune responses to blood-borne antigens, produces antibodies, and clears antibody-mediated pathogens. Some bacteria, in particular encapsulated bacteria, require opsonization to facilitate phagocytosis. In this case, memory B cells located in the spleen produce immunoglobulin M (IgM) that acts as an opsonin to enable the clearance of the polysaccharide-encapsulated bacteria like *Streptococcus pneumoniae*, *Neisseria meningitides*, *Haemophilus influenza* and *Streptococcus pyogenes* [1, 2]. Therefore, splenectomised individuals, with less memory B cells, are at lifelong risk of developing severe septic complications, which can potentially result in “overwhelming post-splenectomy infection (OPSI) syndrome” [3, 4]. While OPSI is relatively rare, with an incidence rate amongst splenectomised individuals of 0.13 per 100 person-years, it can rapidly progress from a mild flu-like illness to a fulminant sepsis with high mortality [4–6]. Due to this increased risk, splenectomised patients require regular vaccinations and, depending on national guidelines, a temporary or permanent commitment to prophylactic antibiotics [7].

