## Methods

### Study design

The study is an international multicentre, open-label, randomized controlled trial with parallel groups. Patients are randomized to the intervention (ASI) or control group (splenectomy) at two possible time points: prior to or during surgery. The patients in the control arm are presumed to have no splenic function. In addition, a third group, namely minimally invasive spleen-preserving distal pancreatectomy (SPDP), serves as a control with the assumed normal function of the spleen. The participants will be followed for 7 months and the study will be conducted over a 2-year period. Patients are recruited in six study sites with considerable expertise and a high annual volume in hepato-pancreatico-biliary surgery: The University Hospital Southampton; University Hospitals Birmingham; Morriston Hospital, Swansea (all in the UK); Fondazione Poliambulanza Istituto Ospedaliero in Brescia, Italy; Virginia Mason Medical Center, Seattle; and the Miami Cancer Institute, Miami (both USA).

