**Fig. 2 Fig2:**
[figure not shown]
Schedule of enrolment, intervention and assessments. *If SPDP cannot be achieved, patients will be randomized to DPS with or without ASI

Routine preoperative blood samples are obtained for baseline analysis and fitness to undergo laparoscopic DP is assessed by an anaesthesiologist. In the case of a planned minimally invasive DPS, all patients will receive pneumococcal vaccination, *Haemophilus influenzae *type b conjugate vaccine and meningococcal conjugate vaccine according to national guidelines prior to or after surgery [7].

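### The advice to have no other vaccinations during the study states no exception, and conflicts with the protocol's own post-splenectomy vaccinations whenever a dose falls within the roughly 7-month follow-up

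*Protocol article*

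**What the plan says.** Three sections of the protocol article bear on vaccines other than the study vaccine.

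- **Primary outcome**, after the description of the Typhim Vi injection and the blood samples: "Participants are advised not to have any other vaccinations during the study period". No exception is given, and the period is not defined there.
- **Participants** (text after Fig. 2): "In the case of a planned minimally invasive DPS, all patients will receive pneumococcal vaccination", together with Hib conjugate vaccine and "meningococcal conjugate vaccine according to national guidelines prior to or after surgery".
- **Surgical technique**: "Patients who undergo DPS, independent of ASI, will receive the standard of care according to national post-splenectomy guidelines", which are said to include "lifelong prophylactic antibiotics and yearly influenza immunization".

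The Background gives the reason for this care: "splenectomised patients require regular vaccinations", because of their lasting risk of severe infection.

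On timing, Study design states: "The participants will be followed for 7 months". The two antibody samples are taken "just prior to vaccination 6 months after surgery and 4 to 6 weeks thereafter". Data collection and management allows two weeks either side of the 6-month visit.

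**The concern.** One sentence tells participants to avoid every other vaccine while on study. Two others say that splenectomised participants will be given vaccines, some of which may be due in that same time. Nothing in the article says which statement gives way, or limits the advice to the weeks around the Typhim Vi injection.

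Safety is the main stake. The advice is addressed to participants. Someone who has lost the spleen and takes it at its word could decline a vaccine that the article counts as standard care.

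Interpretation is the lesser stake. The primary outcome is itself a response to a vaccine. Six sites in three countries, each working to national guidelines, may settle the conflict in different ways. Other vaccine exposure before the Vi challenge could then vary between patients for reasons that nobody has recorded.

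**Working it through.** The plan gives no figure on this point, and the sample size does not depend on it. The check is a comparison of the statements, with simple arithmetic on timing.

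**1. How long is the window?** Inputs: first sample at 6 months, visit range of 2 weeks either side, second sample 4 to 6 weeks later. Take 6 months as 26 weeks and one month as 52/12 = 4.33 weeks.

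- Earliest second sample: 26 − 2 + 4 = 28 weeks, and 28/4.33 = 6.5 months after surgery.
- Latest second sample: 26 + 2 + 6 = 34 weeks, and 34/4.33 = 7.8 months.

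This agrees with the stated 7 months of follow-up.

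**2. What does *study period* cover?** The Primary outcome section does not define it. Data collection and management uses the same term for the time in which the treating centres follow patients up, which points to the whole of follow-up and not only to the interval between the two samples.

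**3. Other than what?** Typhim Vi is the only vaccine named in the Primary outcome section, so the natural reading is any vaccine except Typhim Vi. An exemption for the guideline vaccines would have to be supplied by the reader.

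**4. Which doses conflict?**

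- Pneumococcal, Hib or meningococcal dose before surgery: no conflict, unless the study period is taken to start before surgery.
- The same doses after surgery but before the second sample: conflict.
- Yearly influenza dose due within those 28 to 34 weeks: conflict.
- Yearly influenza dose due outside them: no conflict.

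**5. How often could the influenza overlap arise?** The article gives no dates, so this is an illustration only. Assume one dose a year on a fixed calendar date and surgery dates spread evenly over the year. The chance that the dose is due between surgery and the second sample is then 28/52 = 54% to 34/52 = 65%. Of the 30 patients first planned for randomisation, that is 0.54 × 30 ≈ 16 to 0.65 × 30 ≈ 20. If *study period* meant only the 4 to 6 weeks between the samples, the chance would be 4/52 = 8% to 6/52 = 12%, or about 2 to 4 of the 30. The total sample was later raised to 55, but the article does not say how the added patients are divided between the groups.

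**6. Does it touch the randomised comparison?** Surgical technique applies the same care with and without ASI, and the advice in Primary outcome goes to everyone. The text therefore sets up no difference between the ASI and DPS arms. The guideline vaccinations are described only for DPS patients, so other vaccine exposure may differ between them and the SPDP reference group, which is not randomised.

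**The case against.** The strongest reply is that the sections can be read together. The guideline vaccines may be given before surgery, and a yearly influenza dose need not fall within a window of about 7 months. The sentence in Primary outcome is advice, it stands beside the Typhim Vi procedure, and *other* could mean vaccines beyond those the protocol provides. Much of this stands as a limit on the size of the conflict. It does not remove the conflict: doses after surgery are expressly allowed for, and the exemption that would make the text consistent is not written. Even the narrowest reading of the period leaves influenza doses due between the two samples.

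A reader might infer more than the article supports, in four ways.

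- *That the instructions can never all be followed.* They can, for a patient whose guideline doses precede surgery and whose influenza dose is due outside follow-up.
- *That patients splenectomised after a failed SPDP are left without vaccination cover,* because the Participants section speaks only of planned DPS. The care described in Surgical technique is for all who undergo DPS, which includes them.
- *That the primary comparison is biased.* The wording is identical for both randomised arms.
- *That the Vi response is shown to be distorted.* Nothing in the article shows that these other vaccines change the Vi-specific antibody ratio.

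It is also fair to say that differences between sites follow in part from differing national guidelines, and that a DPS–SPDP difference follows from splenectomy care itself. Both would remain after the wording is corrected. Detailed vaccination schedules and case report form fields may well be in the full protocol, so their absence here is not part of the point. The point is that statements present in the article disagree.

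**Conclusion.** The contradiction is real but limited. It applies to DPS patients in either randomised arm who have a guideline or influenza dose due between surgery and the second blood sample. How many that is cannot be known from the article. For influenza alone, the even-spread assumption gives roughly half to two thirds of DPS patients if the study period means all of follow-up, and about one in ten if it means only the sampling interval.

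The consequence that needs action is for participants: followed literally, the advice could lead a splenectomised person to forgo care that the same article says they will receive. The randomised ASI versus DPS comparison is not biased by this alone, and the effect on Vi titres cannot be quantified from the documents. Uneven vaccine exposure matters mainly when either DPS group is set against SPDP.

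The conclusion rests on two readings: that *study period* means follow-up, as the article's own use of the term suggests, and that *other* means other than Typhim Vi.

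**What to change.** The clinical leads should reconcile Participants, Surgical technique and Primary outcome into one consistent vaccination instruction. It should define the period that it covers, and it should apply by name to all DPS patients (planned or after failed spleen preservation) and to SPDP patients. It should go to all sites and to participants still in follow-up. Which vaccination rule is right is a clinical decision, and none is proposed here.

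As an option, record the type and date of each vaccination up to the second blood sample and tabulate these by group. The follow-up question described in Data collection and management asks about medication that affects the immune system and does not mention vaccines.

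The cost is a protocol clarification and a letter to sites and participants, plus one case report form field and one table if the option is taken. The sample size and the primary analysis do not change.

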### Secondary outcome

Intraoperative details (including operation time, estimated blood loss, blood transfusion), length of hospital stay, readmission rate, morbidity and mortality are the secondary outcomes. All complications are scored using the Clavien-Dindo classification of surgical complications [33].

### Data collection and management

Patient’s details will be de-identified and coded, and randomization will be performed in Castor (Castor EDC, Amsterdam, The Netherlands). Electronic data will be stored in eCRFs (Castor EDC, Europe-based server) and only research team members can access the CRF according to their rights given. Informed consent forms are collected in the study folder. Variables will be collected during study visits except the antibody count after 6 and 7 months, respectively, as these samples are processed altogether after all patients have completed the 7-month study visit. Only the principal investigator and the study coordinator will have access to the final data set. During the study period, patients are strictly followed up by the treating centres. All data produced by this study are considered confidential and will be handled according to the Data Protection Act 2018. All essential documents including source documents will be retained for a minimum period of 5 years following the end of the study by the study sites.

During the follow-up visits, participants were asked whether they were taking other medication that has an impact on the immune system. Adherence to the procedure to implant splenic tissue was ensured by an educational video and precise written instructions. Adherence was assessed by providing details about the number, size and weight of the implanted splenic fragments.

To improve participant retention, follow-up visits were scheduled prior to discharge, and for the 6-month follow-up, a range of ± 2 weeks was allowed. Patients were actively approached prior to the follow-up visits to confirm the date and time of the visit.

### Statistical analysis

For comparison of normally distributed continuous variables, the independent samples t-test will be used and values will be expressed as means and standard deviation. Continuous non-normally distributed variables will be compared using the Mann–Whitney *U* test and values will be expressed as medians (interquartile ranges). Categorical variables will be compared by chi-square or Fisher’s exact test as appropriate, and values will be expressed as proportions. A two-tailed *p*-value < 0.05 will be considered statistically significant. Risk ratios with 95% confidence intervals will be reported. Analysis of the outcomes will be performed based on the intention-to-treat (ITT) population. All randomized participants with an available antibody count will be included in the final analysis in the group they were assigned to. Missing data will not be imputed. The data from patients that do not complete the study will also be analysed. No additional subgroup analyses are planned. All data will be analysed using SPSS (IBM SPSS Statistics for Windows, version 26.0, Armonk, NY, USA).

### Oversight and monitoring

The trial steering committee from the coordinating centre consists of the principal investigator, a senior researcher from the University of Southampton and the trial coordinator. It oversees screening and patient enrolment, progression of the trial and monitors subject drop-out. During the set-up of the trial, the group met weekly and during the initial enrolment phase every 2 to 4 weeks. Monitoring visitations will be scheduled at an appropriate frequency. These visits will be conducted to evaluate the progress of the study, to ensure that the rights and well-being of the subjects are protected, to check that the reported clinical data are accurate, complete and verifiable from source documents, and if the conduct of the study is in compliance with the approved protocol with amendments and Good Clinical Practice. An independent data safety monitoring board (DSMB) will be formed and in the event of serious adverse events (SAEs) which may be related to the study, the DSMB will meet to review the data and advise the steering committee. The DSMB consists of the clinical experts and one senior statistician. Due to the small sample size and the planned analysis of the blood samples after the last follow-up, no interim analysis is planned. The trial will be stopped prematurely if there are serious safety concerns that might be related to any study-specific procedure, especially omental abscess formation within 30 days after the operation and consequent sequelae.

Random audits of trials by the sponsor by an independent auditing committee are allowed.

### Ethics

The conduct of the study will conform to the principles of the Declaration of Helsinki and relevant ethical guidelines. Ethical approval has been obtained from the South-Central Hampshire Research Ethics Committee (reference number 18/SC/0364). All substantial and non-substantial amendments will be submitted to an integrated research application system for approval by all relevant offices. Prior to any study-specific procedure, informed consent will be sought from all patients. On the consent form, participants are asked if they agree to use of their data should they choose to withdraw from the trial. Participants will also be asked for permission for the research team to share relevant data with people from the universities taking part in the research or from regulatory authorities, where relevant. Within this trial, no biological specimens are collected for storage.

There is no anticipated harm and compensation for trial participation. Post-trial care takes place according to centre-specific surveillance protocols.

The study data and statistical code will be available from the corresponding author on reasonable request, as is the full protocol. Results will be disseminated to participants, researchers and healthcare professionals through presentations at international and local conferences and online. Publication in a peer-reviewed scientific journal is planned with authorships for researchers of participating centres. The researchers declare no conflict of interest.

### Patient and public involvement

During the review of the initial protocol, patient representatives appointed by the funder provided input. The patient information sheet and informed consent form were reviewed by public and patient representatives and the research design was discussed. It was emphasized it would be most important to combine the research visits with regular follow-up visits to reduce the burden of study-related procedures.

## Discussion

Sequelae of splenectomy can be devastating and lethal [3, 4]. Whenever possible, splenic preservation after trauma or elective abdominal surgery should be attempted [20]. If splenic preservation cannot be achieved, the only potential way to preserve splenic function is ASI. Several centres have published case series of ASI in trauma patients, showing their positive experience in terms of safety and feasibility [23, 34]. However, splenic function measurements have not been carried out extensively and there is a lack of standardized reporting on how to measure the function of the spleen [26, 35, 36]. Mimicking an infection caused by encapsulated bacteria through vaccination, followed by measuring the specific antibody response, seems the most realistic surrogate outcome to assess splenic immune function. In this randomized trial, we assess splenic immune function using immunoglobulin count in response to a *Salmonella typhi* vaccination. The Typhim Vi™ polysaccharide vaccine was chosen over the non-conjugated Pneumovax 23® because of cross-reacting and different immunogenicity towards different serotypes and high pneumococcal pre-immunization levels in the population have been described, Whereas, the level of endemic infection with *Salmonella typhi*is lower [37, 38]. The newly developed *Salmonella typhi*Vi IgG ELISA measures the response to the Typhim Vi™ polysaccharide vaccine and allows quantifying the specific production of antibodies in response to the vaccination with higher power for discrimination than the Pneumovax 23® [29].

The decision to include only patients who are allocated to undergo minimally invasive surgery was made based on the following rationale: every surgery is an insult to the human body and, therefore, generates an inflammatory response. It has been suggested by several studies that the minimally invasive approach initiates less of an inflammatory response as compared to the open approach [39–42]. Hence, we felt that including only patients who will have minimally invasive surgery creates a more homogeneous study population and a fairer comparison.

There are some potential limitations to this study. First, we use only one measurement to assess splenic function. Nevertheless, we believe that the evaluation of the clearing function is clinically most relevant. Similarly, we intended to reduce additional radiation exposure to a minimum and eschew scintigraphy. As used in prior studies, post-ASI scintigraphy, in our opinion does not adequately reflect splenic function but rather only provides information that splenic tissue is present. Secondly, antibody titres will be assessed at the end of the study; therefore, interim analysis will not be performed, and futility of our interventions will be recognized only at the end of the study. However, clear stopping guidelines were based on the occurrence of postoperative SAEs. Finally, blinding of surgeons, patients and ward staff was deemed impossible due to the nature of the study.

To conclude, the results of this study may give details about splenic immune function after ASI and guide further treatment options for patients where splenectomy cannot be avoided. If splenic immune function can be preserved and the procedure is safe in an elective setting, ASI could become an alternative to the more demanding and time-consuming SPDP. Finally, if the immunologic function of the spleen is restored with ASI, prophylactic antibiotics for splenectomised patients may become obsolete resulting in huge cost saving.

